**Methods and analysis:**

A total of 72 patients with MwoA and 72 healthy controls (HCs) will be enrolled in this study. Resting-state structural and functional magnetic resonance imaging (MRI) data will be collected from each participant at baseline. Patients with MwoA will undergo 12 sessions of acupuncture treatment for 8 weeks, twice per week in the first 4 weeks and once per week for the last 4 weeks. The follow-up will be 12 weeks. The number of days with migraine, frequency of migraine attacks, and average visual analog scale scores will be recorded in detail at weeks 0, 4, 8, 12, and 16 and at the end of follow-up (week 20). The positive response rate will be calculated as the proportion of patients with ≥50% reduction in the number of migraine days during follow-up compared with baseline. Machine learning methods will be applied to classify patients with MwoA and HCs and predict patients with response or non-response to acupuncture treatment based on multimodal MRI parameters, such as gray matter volume, regional homogeneity, amplitude of low-frequency fluctuation, fractional anisotropy, and mean diffusivity.

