Patients with MwoA show widespread structural and functional changes in cortical and subcortical brain regions (19, 20). Acupuncture can potentially alleviate brain dysfunction in migraineurs in a specific way (21–24). Some studies have used either structural or functional parameters of different brain regions to predict the efficacy of verum or sham acupuncture treatment for chronic pain diseases (18, 25–27), demonstrating that objective neuroimaging parameters can be used to predict the analgesic efficacy of acupuncture treatment in patients with migraine.

The aim of this study is to identify brain features detected by multimodal MRI that can be used to predict the response to acupuncture treatment. To this end, multimodal MRI indicators from patients with MwoA and healthy controls (HCs) will be analyzed, then an advanced multivariate pattern analysis (MVPA) based on support vector classification (SVC) will be conducted through training, validation, and testing approach to classify migraineurs and HCs. Responders and non-responders of acupuncture treatment for patients with MwoA will be identified by the clinical outcomes obtained before vs. after treatment. The efficacy of acupuncture will be predicted by support vector regression (SVR) based on multimodal MRI data detected at baseline.

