#### Classification and prediction using machine learning methods

Multivariate pattern analysis (34) will be carried out to classify migraineurs and HCs; this will include feature selection, model construction, and performance evaluation. Principal component analysis (35) will be performed and the searchlight algorithm (36) will be used to select features from multimodal parameters of brain regions, such as gray matter volume (GMV), ReHo, ALFF, fALFF, FA, and MD. The linear kernel support vector classification will be used to construct the classification model (37), which will be assessed by leave-one-out cross-validation (LOOCV). Clusters with a minimum accuracy of 70% will be identified as meaningful classifying features.

Patients with MwoA will be divided into the response and non-response groups (defined as ≥50% and <50% reduction, respectively, in the number of migraine days end of treatment compared with baseline). Support vector regression will be performed to discriminate between the response and non-response groups using the abovementioned classifying features of brain regions (ie, GMV, ReHo, ALFF, fALFF, FC, FA, and MD) (38). In addition to neuroimaging features, we may combine multidimensional features such as clinical data to build the model. After constructing the prediction model for patients with MwoA, LOOCV will be performed to evaluate the robustness of the model. A receiver operating characteristic (ROC) curve will be generated, and the area under the curve (AUC, 0–1) will be calculated to assess the power of the model. The performance of the SVR model will be quantified by calculating sensitivity and specificity based on the number of true positives and true negatives.

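### The MwoA-versus-HC accuracy of clusters kept by the 70% rule will be optimistic, because the analysis section omits the testing step that the Introduction announces

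*Protocol article*

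**What the plan says.** The Abstract fixes the only sample: "A total of 72 patients with MwoA and 72 healthy controls (HCs) will be enrolled in this study".

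The Introduction says that the support vector classification analysis "will be conducted through training, validation, and testing approach to classify migraineurs and HCs".

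The section on classification and prediction using machine learning methods is the only operational description. Its order is:

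1. PCA is performed, and "the searchlight algorithm (36) will be used to select features from multimodal parameters of brain regions".
2. A linear-kernel support vector classifier separates patients from controls and is assessed by LOOCV.
3. The next sentence is the retention rule: "Clusters with a minimum accuracy of 70% will be identified as meaningful classifying features".
4. The kept features go forward: "Support vector regression will be performed to discriminate between the response and non-response groups using the abovementioned classifying features of brain regions".
5. For that second model, "After constructing the prediction model for patients with MwoA, LOOCV will be performed to evaluate the robustness of the model".

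The section describes no split, held-out sample, external sample or nesting of selection within the LOOCV folds.

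**The concern.** The two sections describe different validation designs for the same classification. The Introduction has a testing step and the analysis section has none.

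The 70% sentence directly follows the LOOCV sentence, and no other source of accuracy is described. The natural reading is that a cluster is kept when its LOOCV accuracy in the 144 participants reaches 70%, and that this same accuracy then describes how well it classifies. A cluster chosen because its estimate was high will, on average, have a lower true accuracy. LOOCV does not correct for this, because every held-out participant also helped decide which clusters were kept.

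Two things are at stake. One is the stated MwoA-versus-HC accuracy, together with the list of regions called meaningful. The other is the input to the responder model, since partly lucky clusters bring noise into a model fitted to 72 patients.

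**Working it through.** **No plan figure to reproduce.** The 70% is a threshold. The article derives neither an accuracy nor a sample size, so the check asks how the threshold behaves at the planned numbers.

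**Inputs from the article:** 72 patients and 72 controls (n = 144); cut-off 70%; LOOCV as the only assessment. **Assumed, because not given:** number of clusters, features per cluster, true signal.

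**Step 1. The cut-off as a count.** 0.70 × 144 = 100.8, so at least 101 of 144 must be correct.

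**Step 2. Chance that one cluster passes.** Treating the 144 predictions as independent, P(X ≥ 101) with X ~ Binomial(144, p):

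| True accuracy p | P(pass) |
|---|---|
| 50% (noise) | 0.00000074 |
| 55% | 0.00014 |
| 60% | 0.0075 |
| 65% | 0.113 |

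**Step 3. Expected number kept = number of clusters × P(pass).**
- Noise, 100,000 clusters: 100,000 × 0.00000074 = 0.07.
- Noise, 300,000 clusters: 0.22 (using the unrounded probability).
- True accuracy 60%, 2,000 clusters: 2,000 × 0.0075 = 15.

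Noise seldom passes. Weak clusters pass in useful numbers when many are searched, and each is then credited with at least 70%. Simulated noise agrees: with 20,000 clusters and 6 runs per setting, none reached 70%, and the mean maximum was 66% to 68%.

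**Step 4. Size of the optimism.** Simulation of 72 versus 72 with independent clusters of 5 features, one of which separates the groups by the stated SD. Every cluster carries this signal. A linear least-squares (ridge) classifier stands in for the linear SVC. LOOCV is exact, clusters are kept at 70% or more, and kept clusters are then scored in 1,000 new subjects (15 runs per row).

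| True separation; clusters | Mean LOOCV, all clusters | Kept: LOOCV | Kept: new subjects | Excess (points) |
|---|---|---|---|---|
| 0.3 SD; 5,000 | 52.4% | 70.7% | 55.3% | 15.4 |
| 0.5 SD; 2,000 | 56.9% | 71.0% | 58.5% | 12.5 |
| 0.6 SD; 2,000 | 59.2% | 71.1% | 60.5% | 10.6 |

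A patient-versus-control model combining the kept clusters gave, by LOOCV against new subjects:
- 0.3 SD: 70.9 − 55.9 = 15.0 points
- 0.5 SD: 83.7 − 69.2 = 14.5 points
- 0.6 SD: 96.3 − 85.9 = 10.4 points

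In the 0.3 SD row only 60% of runs kept any cluster.

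A second, smaller simulation (500 searchlights of 10 voxels, 200 of them active, effect 0.4 or 0.5 per voxel) points the same way. Kept clusters showed 71.4% against 59.2% and 71.3% against 61.7%, an excess of 12.2 and 9.6 points. It is thin: only 1 and 4 of 5 runs had a passing cluster.

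**Step 5. Does the selection leak into the responder model?** Clusters were selected on the patient/control label as above. A response label unrelated to the features was then assigned to the 72 patients. The LOOCV AUC averaged 0.47 in both the 0.5 and 0.6 SD settings. In the 0.3 SD setting, with few usable runs, it was lower still (0.26). None shows upward bias.

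**The case against.** The strongest reply has three parts.

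**The 70% is not defined.** The article never says that it is LOOCV accuracy in all 144 participants, nor that selection sits outside the folds. A condensed article may leave fold-level detail to the full protocol, and the Introduction's wording is compatible with selection inside training data. This stands as a limit: the reading is inferred from adjacent sentences. It does not remove the point, because the article states two validation designs and the operational one lacks the announced testing step. A reader might infer that the trial has no test set at all. The text supports only that none is described in the analysis section.

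**The responder model is not circular by this route.** A reader might infer that its AUC, sensitivity and specificity are inflated too, since the kept clusters feed it and it is judged by LOOCV in the same patients. The documents do not support that. Clusters are kept on the patient/control label, the responder model is scored on reduction in migraine days, and Step 5 finds no upward bias. It would become circular only if features, clinical variables or tuning were chosen on the response label outside the folds. The article leaves room for this by allowing clinical data to be added.

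**The cut-off is strict against noise.** This is correct (Steps 2 and 3). Simulations that pick the best 10 to 50 of 5,000 noise features on all 144 participants report 79% to 92% by LOOCV, but that is a best-of-many rule, not this plan's fixed cut-off. Nor do the kept clusters become useless: in Step 4 they still classify new subjects above chance.

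**Conclusion.** The point holds for the patient-versus-control classification. Followed as written, the machine learning section yields an optimistic MwoA-versus-HC accuracy for the kept clusters and for any patient-versus-control model that combines them. The article does not itself describe such a combined model; the only model that it builds on the kept clusters is the responder regression.

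The excess is roughly 10 to 15 percentage points. This rests on assumed signal strength, cluster number, independent clusters and a stand-in linear classifier, so it shows direction and rough size rather than a forecast. It also rests on reading the 70% as LOOCV accuracy in all participants. The mismatch between the Introduction and the analysis section needs no such assumption.

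The point does not extend to a claim that the rule manufactures regions from noise, or that the responder results are inflated by this selection.

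**What to change.** Reconcile the Introduction with the machine learning section in one of two ways:

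- **Nested cross-validation.** Repeat scaling, PCA, searchlight selection, the 70% cut-off and classifier tuning inside each outer training fold. LOOCV can remain the outer loop.
- **A held-out test set.** Define it before analysis and keep it out of all selection and tuning.

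In either case, state which accuracy the 70% refers to, and report only the outer-loop or test-set accuracy for MwoA versus HC. Apply the same rule to the responder model: any feature, clinical variable or tuning value chosen on the response label must be chosen inside the training folds.

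The nested version needs no additional participants or scans, only wording and computing time. A held-out set also reduces the number available for training. Either way the reported accuracies will be less favourable. With 15 patients recruited when the article was written, the change can be fixed before the analysis.

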### Patient safety

Routine examination of blood, urine, and stools; blood biochemical testing (including liver and kidney function); and electrocardiography will be performed for each participant before trial enrollment. Adverse events caused by acupuncture, such as bleeding, hematoma, pain, and needle-related fainting, will be recorded in detail in the CRF. Severe adverse events such as death, life-threatening disability, or the need for hospitalization will be reported to the project leader, the research institute, and the ethics committee within 24 h and will be documented in the CRF.

### Quality control

Diagnostic, inclusion and exclusion criteria will be strictly applied to screen participants. Patients with MwoA and HCs will be matched in age and education, and patients with average headache VAS scores at baseline >3 will be included. Before the study, the acupuncturists will undergo standardized training and will be required to strictly control the manipulation of the acupuncture needle to minimize interindividual differences. MRI data collection will be carried out according to the operating procedures and experimental design. Communication with patients will be controlled to minimize the influence of the environment and other factors.

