## Methods and analysis

### Study design

This non-randomized clinical trial will enroll 72 patients with MwoA and 72 with HCs. The study will last 24 weeks including a 4-week baseline period; for migraineurs, this will be followed by an 8-week treatment period and a 12-week follow-up period (Table 1). Structural and functional MRI scans will be performed at baseline. Clinical outcomes will be evaluated after treatment and during the follow-up. Figure 1 shows a flow diagram of the study. This protocol is reported in accordance with Consolidated Standards of Reporting Trials and Standards for Reporting Interventions in Clinical Trials of Acupuncture. The protocol was approved by the Institutional Review Board and Ethics Committee of the Hospital of Chengdu University of Traditional Chinese Medicine (approval no. 2020KL-058) and is registered with the Chinese Clinical Trial Registry (registration no. ChiCTR2100042915).

**Table 1 T1:** Standard protocol items: recommendations for interventional trials (SPIRIT) schedule of the trial.

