### Participants

Seventy-two patients with MwoA and 72 with HCs will be recruited for this study. Inclusion criteria for patients with MwoA are as follows: (1) aged 18–60 years; (2) right handed; (3) diagnosed with MwoA according to the 2018 International Classification of Headache Disorders (ICHD-3) (1); (4) have a history of migraine for over 6 months; (5) have had migraine attacks 3–15 times per month in the past 3 months; (6) did not take prophylactic headache medicine or receiving acupuncture treatment in the previous 3 months; and (7) signed the informed consent form.

Exclusion criteria were as follows: (1) suffering from psychiatric, neurologic, cardiovascular, respiratory, or renal illness; (2) suffering from any other chronic pain conditions or have a history of head trauma with loss of consciousness; (3) alcohol or drug abusers; (4) are pregnant or lactating; (5) have acupuncture contraindications such as bleeding tendency; and (6) have MRI contraindications such as claustrophobia.

Inclusion criteria for HCs are as follows: (1) aged 18–60 years; (2) right handed; and (3) free of any diseases. HCs will be excluded if they meet the following criteria: (1) have drug or alcohol addiction; (2) have contraindications for MRI; and (3) pregnant or lactating.

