### Participant recruitment

All MwoA patients and HCs will be recruited as outpatients and inpatients of the Neurology Department of the Hospital of Chengdu University of Traditional Chinese Medicine or from the community through advertising from March 2021 to December 2023.

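### Controls are matched to patients on age and education but not on sex, so a sex imbalance could inflate the patient-versus-control classifier and affect which features are selected

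*Protocol article*

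**What the plan says.** The design is non-randomized: "This non-randomized clinical trial will enroll 72 patients with MwoA and 72 with HCs". The only stated protection of the patient-control contrast against demographic differences is in Quality control: "Patients with MwoA and HCs will be matched in age and education".

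Under Participants, the control inclusion criteria are "1) aged 18–60 years; (2) right handed; and (3) free of any diseases". There is no sex criterion or quota for either group. Women can enter both groups, since pregnancy or lactation is an exclusion for patients ("4) are pregnant or lactating") and again for controls. Participant recruitment gives one list of sources for patients and controls together: the hospital's neurology department, "or from the community through advertising from March 2021 to December 2023". Sex or gender is not mentioned anywhere in the shown text.

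The machine learning section states that "The linear kernel support vector classification will be used to construct the classification model", that leave-one-out cross-validation (LOOCV) assesses it, and that the plan will "select features from multimodal parameters of brain regions, such as gray matter volume (GMV), ReHo, ALFF, fALFF, FA, and MD". Clusters reaching 70% accuracy count as meaningful. These classifying features then feed the model that separates responders from non-responders.

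**The concern.** A linear classifier uses any signal that separates the two groups. If the groups differ in sex mix and an imaging measure differs by sex, that measure helps tell patients from controls whether or not it has anything to do with migraine. Gray matter volume, which can vary with head size, is a plausible example.

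Cross-validation offers no protection. The held-out participant comes from the same two groups with the same imbalance, so the confound predicts as well in the held-out case as in the training data.

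Two things are at stake. One is the reported accuracy for migraine versus health. The other is the list of clusters that pass the 70% rule, because that list supplies the imaging features of the response model and will be interpreted as migraine-related brain regions.

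**Working it through.** The plan has no figure of its own to reproduce: it gives no sex shares, sex effects or expected accuracy. What follows is an illustration.

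**Inputs from the protocol article.** 72 patients and 72 controls (Study design); matching on age and education (Quality control); 70% accuracy rule (machine learning section). If accuracy is counted over all participants, 0.70 × 144 = 100.8, so a cluster must classify at least 101 of 144 correctly.

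**Assumed inputs.** Female shares in each group, the accuracy *q* with which a cluster decodes sex, and effect sizes in SD units.

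**Step 1: accuracy from sex alone.** With equal groups, calling every woman a patient and every man a control gives

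accuracy = 0.5 + (female share in patients − female share in controls)/2.

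This is an upper bound, because the classifier sees images and not sex. If a cluster decodes sex with accuracy *q*, the gain over 0.5 is multiplied by (2*q* − 1).

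| Female share, patients vs controls | *q* = 1 | *q* = 0.9 | *q* = 0.8 |
|---|---|---|---|
| 75% vs 75% | 0.500 | 0.500 | 0.500 |
| 75% vs 60% | 0.575 | 0.560 | 0.545 |
| 75% vs 50% | 0.625 | 0.600 | 0.575 |
| 80% vs 50% | 0.650 | 0.620 | 0.590 |
| 80% vs 40% | 0.700 | 0.660 | 0.620 |

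The gap needed to reach 70% is 0.4/(2*q* − 1): 40 points at *q* = 1, 0.4/0.8 = 50 points at *q* = 0.9, and 0.4/0.6 = about 67 points at *q* = 0.8.

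**Step 2: chance of passing the 70% rule.** Treating LOOCV predictions as independent, the binomial probability of at least 101 correct out of 144 for one cluster is about 7 × 10⁻⁷ at true accuracy 0.50, 0.034 at 0.625 and 0.113 at 0.65. A searchlight examines many clusters, so accuracies below 70% still matter.

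**Step 3: sex added to a real but weaker signal.** For one normally distributed feature, accuracy = Φ(shift/(2 × SD)). The shift is the migraine effect plus the sex effect times the gap in female share. The variance is 1 plus the squared sex effect times the average of *p*(1 − *p*) over the two groups. Take 75% female patients and a sex effect of 1 SD.

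| Migraine effect | No gap | 25-point gap | 40-point gap |
|---|---|---|---|
| 0 | 0.500 | 0.545 | 0.572 |
| 0.5 SD | 0.591 | 0.633 | 0.659 |
| 0.8 SD | 0.643 | 0.683 | 0.707 |

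For the 0.8 SD feature with a 40-point gap: shift = 0.8 + 1 × 0.4 = 1.2; variance = 1 + (0.1875 + 0.2275)/2 = 1.2075; SD = 1.099; Φ(1.2/2.198) = 0.707. That feature fails the rule with sex balanced and passes it with the imbalance. With no migraine effect, a single feature of this kind stays well below 70%.

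**Step 4: how a gap could arise.** If both groups came from one 75%-female source, the SD of the difference would be √(2 × 0.75 × 0.25/72) = 0.072. By simulation, a gap of at least 10 points occurs by chance in about 15% of studies, and one of at least 20 points in about 0.5%. A large gap would therefore need recruitment that differs between the groups.

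**The case against.** There are four serious counter-arguments.

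*The groups may not differ.* A reader might infer that patients come from a clinic and controls are volunteers, so the sex mix must differ. The document does not say so: it lists the same sources for both groups. This stands, and a differing mix is possible but not established. Still, controls must be free of disease, which may shift them towards community recruitment, and the stated rule would not prevent a resulting gap.

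*The 70% figure is a best case.* It is tempting to say that sex alone would already qualify as a meaningful feature. That takes an assumed 40-point gap and perfect decoding of sex from one cluster, and the rule applies to imaging clusters, not to the sex variable. This also stands. The more plausible effects are inflated accuracy and borderline clusters pushed over the line.

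*The response model is not contaminated as such.* A reader might infer that the imbalance produces false prediction of response. It does not, because that model is fitted within patients and controls contribute nothing to its AUC, sensitivity or specificity. If sex were related to response, a sex-linked feature would carry real predictive information, though it could be mislabelled as a migraine feature.

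*Adjustment may be specified elsewhere.* Covariate regression and intracranial-volume correction are details that a condensed article commonly leaves to the full protocol or analysis plan. Their absence here is no finding. The matching list, however, is an explicit statement, and poor sex overlap fixed at recruitment cannot be fully repaired by later analysis.

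**Conclusion.** The point holds in limited form. The stated matching rule omits sex in a non-randomized comparison open to both sexes, and nothing in the stated recruitment balances it. The patient-versus-control classifier and the selection of clusters are therefore open to sex confounding that LOOCV cannot reveal.

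The size depends on a sex gap, a sex effect and a decoding accuracy that the document does not give. Gaps of 15 to 30 points in the assumed examples allow sex alone at most 57.5% to 65%, less if decoding is imperfect. For the response model, the consequence is confined to which features enter and how they are interpreted. Severity is moderate. Confidence is high that sex is missing from the matching factors and moderate that this will matter.

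**What to change.** Add sex to the matching factors in Quality control: frequency-match the 72 controls to the patients by sex as well as age and education, and report sex by group. With equal female shares, accuracy from sex alone returns to 0.500 whatever the sex effect on the images.

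As a low-cost check, report the accuracy of a classifier that uses only sex, age and education, so that the imaging accuracy can be read against it. If residual imbalance remains, adjust the features for sex with the adjustment fitted inside each training fold.

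The sample size does not change. The cost is slightly slower control recruitment. The Trial status section reports 15 patients recruited, with recruitment running to December 2023, so the change was feasible at that stage. The number of controls already enrolled is not given; any remaining control recruitment can be directed to close a gap.
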